### Exploratory objectives

#### The key exploratory objectives are the following:

To assess the time until the first and second subsequent systemic therapy after study SURF outputTo identify the clinical and biological factors associated with DOT, PFS, and OSTo identify tissue biomarkers potentially linked to the activity of sunitinibTo identify blood biomarkers related to the activity and/or toxicity of sunitinibTo assess the impact of body mass index (BMI) on activity-related parameters of sunitinib

### Characteristics of participants

#### Key inclusion criteria are the following:

Men or women over 18 years oldPatients with local, advanced, or inoperable or metastatic RCC who are starting first-line treatment with sunitinib 50 mg (4/2 weeks’ regimen) according to the marketing authorization indicationPatients with histologically or cytologically confirmed renal cancer clear cell variant or with a clear cell componentKarnofsky performance status ≥70%Adequate organ function:Absolute neutrophil count ≥1500/μLPlatelets ≥100,000/μLHemoglobin ≥10 g/dLCreatinine clearance ≥30 mL/min (by the MDRD formula)Total bilirubin ≤1.5 × ULN (upper limit of the normal range)AST ≤2.5 × ULN and ALT ≤2.5 × ULN or AST and ALT ≤5 × ULN if with liver abnormalities due to liver metastasesSignature of informed consent for participation

#### Key exclusion criteria are the following:

Renal carcinoma with no clear cell componentPrevious systemic treatment for RCC regardless of type except immunotherapy (including targeted therapy, chemotherapy, or hormone or experimental therapy). Previous or concomitant treatment with a bisphosphonate or denosumab is allowedPatients whose clinical state and comorbidities are not consistent with administration of sunitinib at the initial dose of 50 mg daily with schedule 4/2General contraindication, warnings, and precautions to sunitinib treatment as described in the summary of product characteristics [12]Major surgery within 4 weeks before sunitinib initiationHistory of symptomatic cerebral metastases, spinal cord compression, or meningeal carcinomatosis. Patients with cerebral metastases discovered incidentally on imaging and who are asymptomatic are not excluded if these metastases have been treated (radiotherapy and/or surgery) with a period of at least 4 weeks between the end of treatment and inclusion into the study and no clinical or radiological signs of relapse, and corticosteroid dose is not exceeding 10 mg/day of prednisone or equivalent. Subjects will be excluded if they have signs of grade ≥2 treatment-related complicationsAny of the following features within 3 months of the administration of sunitinib: myocardial infarction, severe/unstable angina, coronary artery/peripheral artery bypass graft, symptomatic congestive heart failure, cerebrovascular accident, or transient ischemic attackPulmonary embolism or deep vein thrombosis within 3 months of inclusion (unless it is stable, asymptomatic, and treated with a low molecular weight heparin for at least 10 days before inclusion)Any known acute or chronic disorder (such as severe chronic obstructive pulmonary disease) which in the opinion of the investigator could impact on the patient’s capacity to receive the study treatment or make interpretation of toxicity or adverse events difficult

### Study procedures and randomization

Patients candidate for first-line treatment with sunitinib and meeting the inclusion/exclusion criteria will be offered participation in the protocol. All the included patients will receive sunitinib 50 mg once daily with schedule 4/2 according to the marketing authorization indication.

When the investigator believes a modification of administration of sunitinib is necessary, the patient will become eligible for randomization. Randomization will take place in all study sites using an IWRS type of centralized system.

Randomization will be performed according to a ratio of 1:1 using minimization technique with stratification according to:centreTime to randomization: time between initiation of sunitinib and dose adjustment (<6 or ≥6 months)Heng prognostic factors at baseline (good and intermediate prognosis groups vs poor prognosis group)

### Clinical measures

At treatment initiation (Fig. 3), data collected will include sociodemographic characteristics, oncologic history, symptoms at baseline, biological abnormalities, tumor assessment report, and evaluation of HRQoL (EORTC QLQ-C30 and EuroQoL EQ-5D questionnaires).

**Fig. 3 Fig3:**
[figure not shown]
Schedule of enrollment, interventions, and assessments in the SURF study

During each cycle of sunitinib before and after randomization (every 6 weeks), data collected will include symptoms and biological abnormalities, toxicities according to NCI CTCAE version 4.0, data related to sunitinib (start date, end date, dosage, dose modification and date, monitoring of compliance), toxicities related to sunitinib with grades according to NCI CTCAE version 4.0, and evaluation of HRQoL.

Tumor assessments will be performed every 12 weeks with evaluation of the response by RECIST 1.1 criteria.

During follow-up, cancer treatments provided later (start and end dates, type of treatment, reasons motivating the choice of treatment), the vital status and death-related data (date and cause), and the date and mode of progression for patients who left the study for reasons other than progression will be collected.

### Collection of biological samples

A blood sample of 10 mL will be collected at baseline only if the centre has the necessary equipment for centrifugation and freezing the plasma. The sample will be centrifuged, and the plasma will be frozen on-site within 4 h at −80 °C. The available samples of the primary tumor and metastases will be collected in this study. No additional biopsy will be performed. The parameters evaluated will be based on immunohistochemistry techniques or tumor somatic genomic sequencing.

### Intervention

#### Control arm

In the control arm (arm 4/2), the sunitinib dose is reduced according to the marketing authorization indication: sunitinib 37.5 mg once daily with schedule 4/2. A treatment cycle includes a period of exposure to sunitinib and a pause period for a total of 6 weeks.

#### Experimental arm

In the experimental arm (arm 2/1), the sunitinib dose is maintained at 50 mg once daily (no modification of the dose) with a modification of the drug administration schedule: 2 weeks on treatment followed by a pause of 1 week. A treatment cycle includes two periods of exposure to sunitinib and two pause periods for a total of 6 weeks.

#### Blinding

An identification code is assigned to each subject included in the study. The list of identification of subjects including the code numbers for the names and full addresses of the subjects included in the trial will be retained by the investigator and will not be available for the promoter.

The subjects will be informed that data resulting from the study will be stored in and analyzed by a computer. In particular, it will be made clear that personal data concerning them will be accessible only to the investigator and inspection by official authorities or quality audit by representatives of the promoter of this data is possible.

#### Treatment duration

Patients participate until sunitinib is permanently discontinued for toxicity reason, progression, or death related to renal cancer or not.

The duration of follow-up after discontinuation of sunitinib will be 2 years. All death-related data will be collected as part of the study.

All patients included in this study can leave the study at any time, without having to justify the reason.

Study discontinuation include:Subject’s request to stop study treatment (withdrawal of consent)Decision of the investigatorTermination of the study by the sponsorAdverse eventsNon-compliance with the protocolProtocol-defined disease progressionLost to follow-upDeath

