### Endpoint definitions

#### Primary endpoint

The primary objective of this study is to estimate the median duration of treatment (DOT) in each treatment group (arm 4/2 vs arm 2/1) calculated from sunitinib initiation (Fig. 2).

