### Follow-up assessments

From treatment initiation, clinical, radiological, and biological data are collected prospectively. Visits are carried out every 6 weeks.

Patients will fill in HRQoL’s questionnaires EORTC QLQ-C30 [13] and EuroQoL EQ-5D [14] every 6 weeks (day 1 of each cycle).

Tumor assessments must be achieved every 12 weeks regardless of treatment cycles. Patients will be monitored for 2 years after discontinuation of sunitinib according to the rhythm of the usual medical care. Any subsequent treatment will be recorded with the date and mode of progression for patients who left the study for reasons other than progression.

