### Analyses of time-to-event data

The median duration of treatment and other survival rates will be estimated using the Kaplan-Meier method. Median survival will be described with their confidence intervals (one-sided statistical test of significance (*α* 5%)) in each of the arms.

Survival curves will be calculated by the Kaplan-Meier method and described using their medians and their 95% confidence intervals.

Multivariate Cox analysis will be conducted to identify factors potentially influencing survival.

All variables originally collected will be tested by univariate analysis. The variables with *P* ≤ 0.20 will be eligible in multivariate analysis.

No *P* value will be indicated, and the effect size of treatment will be assessed using the HR with its confidence interval.

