### Study duration

Up to 20 French sites will be opened for this study to achieve a total of 248 randomized patients (124 patients in each arm).

The main objective of this study is to estimate the DOT by sunitinib according to the administration regimen. The final analysis of the DOT will take place after 112 events. The total duration of the study (between the first inclusion and the final analysis) is estimated to be 60 months.

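### Follow-up that ends 2 years after each patient stops sunitinib censors overall survival at treatment duration plus 24 months, so the Kaplan-Meier tail beyond month 24 is informatively censored and probably too high

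*Protocol article*

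**What the plan says.** Treatment duration sets an individual end of follow-up: "The duration of follow-up after discontinuation of sunitinib will be 2 years". Follow-up assessments says the same: "Patients will be monitored for 2 years after discontinuation of sunitinib according to the rhythm of the usual medical care". Clinical measures (text below Fig. 3) names what is collected during follow-up, including vital status and deaths ("the vital status and death-related data (date and cause").

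Directly after the 2-year limit, Treatment duration adds: "All death-related data will be collected as part of the study". That sentence has no time window.

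OS, by arm and in the whole included population, is among the key secondary objectives (Secondary endpoints). The estimator is given under Analyses of time-to-event data: "The median duration of treatment and other survival rates will be estimated using the Kaplan-Meier method". DOT, the primary endpoint, is "calculated from sunitinib initiation". On when treatment ends, the article says: "Patients participate until sunitinib is permanently discontinued for toxicity reason, progression, or death related to renal cancer or not".

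On the calendar, Study duration says: "The total duration of the study (between the first inclusion and the final analysis) is estimated to be 60 months". Sample size gives 24 months of inclusion.

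**The concern.** Kaplan-Meier requires that patients censored at a given time have the same later risk as those who stay under observation. Here the censoring time is a function of DOT. Patients who stop early, often for progression or toxicity, leave the OS risk set first; those treated for longer remain. If longer treatment goes with longer survival, the patients remaining beyond month 24 are a favourable selection and the curve sits too high.

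Three things are at stake: the late part of the OS curves, by arm and overall; deaths that are never recorded; and equal follow-up between arms. If the experimental schedule lengthens DOT, as the trial hopes, that arm is also observed longer for OS. No analysis plan can recover vital status that was not collected.

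**Working it through.** **Inputs from the article**
- End of follow-up: 24 months after sunitinib stops (Treatment duration; Follow-up assessments).
- Median DOT: 6 months under H0, 8.5 months under H1 (Sample size).
- Inclusion over 24 months (Sample size); 60 months from first inclusion to final analysis (Study duration).

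**Assumptions not in the article**
- DOT is exponential, and OS is counted from sunitinib initiation.
- Median survival after stopping is 12, 18 or 24 months.
- Correlation between DOT and survival after stopping is 0, 0.3 or 0.6 (Gaussian copula).

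**Step 1. The plan's own figure.** A one-sample, one-sided 5% test of a 6-month median, with exponential DOT of median 8.5 months and n = 112, has simulated power 0.796 against the stated 80%. Inflation: 112 × 1.1 = 123.2, so 124 per arm and 248 in total. The planning medians are therefore read as the plan uses them. The present point does not depend on this calculation.

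**Step 2. What the calendar allows.** With 24 months of inclusion and a 60-month study, the last patient could be followed for 60 − 24 = 36 months and the first for 60, whatever their DOT.

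**Step 3. What the written rule allows.** A survivor is observable at month 24 + x only if DOT > x. With median m, P(DOT > x) = 0.5^(x/m).

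| Month | x | Observable if alive, m = 6 | Observable if alive, m = 8.5 |
|---|---|---|---|
| 25 | 1 | 89% | 92% |
| 30 | 6 | 50% | 61% |
| 36 | 12 | 25% | 38% |
| 48 | 24 | 6% | 14% |

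Median potential follow-up is 6 + 24 = 30 months against 8.5 + 24 = 32.5 months. Up to month 24 the rule removes nobody, because a patient alive then is either still treated or stopped less than 24 months earlier.

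**Step 4. Effect on Kaplan-Meier OS.** OS = DOT + survival after stopping (exponential). There were 2 × 3 × 3 = 18 scenarios of 400,000 patients each, with a calendar cut-off uniform over 36 to 60 months. Censoring at min(DOT + 24, calendar cut-off) was compared with true survival.
- With a post-stop median of 18 months, the share at risk at month 36 falls from 36–37% to 14–20% (m = 6) and from 41–43% to 24–29% (m = 8.5).
- Over all 18 scenarios the error is about +0.6 to +4.1 points at month 36 and +1.1 to +11 at month 48.
- Between 10% and 26% of the deaths that a common cut-off would capture are lost.
- Median OS shifts by 0 in all six scenarios with a post-stop median of 12 months and by 0 to 0.5 months in all six with 18 months. The largest shift is at a post-stop median of 24 months, correlation 0.6 and m = 8.5: 38.7 estimated against 34.7 true, or 4.0 months.
- With the common calendar cut-off alone, the error is zero to within 0.1 point in all 18.

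**Step 5. Sensitivity.** A wider grid of 54 scenarios adds Weibull shapes 0.7, 1 and 1.3 after stopping and 5% of patients dying at discontinuation, with no calendar cut-off. The error is 0 at month 24, −0.2 to +1.5 points at month 30, −0.8 to +5.2 at month 36 and −2.2 to +13.9 at month 48. OS at month 36 is overstated in 48 of the 54. The other six combine zero correlation with a falling hazard after stopping and understate it by 0.1 to 0.8 points. Median OS shifts by −0.3 to +2.6 months.

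**The case against.** The strongest counter-argument is the sentence "All death-related data will be collected as part of the study". If it means deaths without a time limit, the 2 years would govern visits only and most of the problem would go. The wording leaves that open, and the full protocol may settle it. But the sentence follows directly on the 2-year limit, and Clinical measures places vital status and death data within follow-up, so the more natural reading is deaths during those 2 years. Even the wider reading supplies no last-known-alive dates for survivors, and these are needed to censor them correctly.

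The second argument is size. With 124 per arm, the binomial standard error at month 36 is already about 4.5 points, so the error there is below sampling noise. The written rule still captures 74–90% of the deaths. OS is a secondary, estimation-only objective, and the article says no P value will be given. All of this stands and limits the weight of the point. It does not remove it: the error is systematic, the confidence interval does not reflect it, and it grows along the tail.

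A reader might also infer more than the article supports:
- **That OS as a whole is overstated.** It is not affected to month 24, and a median at or below 24 months does not move.
- **That survival beyond month 24 rests only on longer-treated patients.** At month 25 some 89–92% of patients are still observable. The selection builds up gradually.
- **That the between-arm hazard ratio is biased by a known amount.** Follow-up would differ by arm if DOT does, but no bias in the hazard ratio has been computed here.

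**Conclusion.** The point holds for OS beyond month 24. As written, follow-up for OS ends at DOT + 24 months, and the loss of observable patients (75% or 62% out of reach by month 36) follows from the rule and the planning medians, given exponential DOT. That the tail is overstated is probable, not certain. Direction and size rest on an association between DOT and later survival, and on survival after stopping, neither of which the article gives. Over the 18 assumed scenarios the error is about 0.6 to 4 points at month 36 and 1 to 11 at month 48. A shift in median OS of about 4 months is the extreme corner; in the 12 scenarios with a post-stop median of 12 or 18 months it is 0.5 months or less.

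The 36 to 60 months available under a common cut-off depend on 24 months of inclusion and on the estimated 60-month duration. Slower inclusion or an earlier final analysis would narrow the gain. This is a worthwhile, low-cost improvement. It does not affect the primary endpoint.

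**What to change.** In Clinical measures, Treatment duration and Follow-up assessments, state that vital status (date of death, or date last known alive) is collected for every included patient, randomized or not, to one common calendar cut-off: the final analysis, about 60 months after first inclusion. Censor OS only at that date or at true loss to follow-up. Make the sentence on death-related data say the same, so that it can no longer be read two ways. The 2-year limit can stay for the other follow-up data.

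The cost is a small amendment and modest extra site work: vital-status checks by telephone or from records for patients more than 2 years past discontinuation, within the study duration already planned.

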### Follow-up assessments

From treatment initiation, clinical, radiological, and biological data are collected prospectively. Visits are carried out every 6 weeks.

Patients will fill in HRQoL’s questionnaires EORTC QLQ-C30 [13] and EuroQoL EQ-5D [14] every 6 weeks (day 1 of each cycle).

Tumor assessments must be achieved every 12 weeks regardless of treatment cycles. Patients will be monitored for 2 years after discontinuation of sunitinib according to the rhythm of the usual medical care. Any subsequent treatment will be recorded with the date and mode of progression for patients who left the study for reasons other than progression.

### Statistics and data analysis

#### Sample size

The main objective of this randomized phase II trial is to evaluate the median DOT in each arm.

TThe following hypotheses will be tested: H0 (null hypothesis of inefficiency): median DOT of 6 months [15, 16] and H1 (alternative efficiency hypothesis): median DOT of 8.5 months. A Brookmeyer-Crowley type of test will be used to estimate the median. With a one-sided statistical test of significance (*α* 5%) and a power of 80%, it will be required to include 112 patients in each arm for 24 months with at least 12 months of follow-up.

The approximate upper critical value to reject H0 is 7.66 months. The number of patients is increased by 10% to take account of the potential progression or treatment discontinuation by patients before randomization and patients lost to follow-up. It will therefore be necessary to include 248 patients.

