**Methods/design:**

SURF [NCT02689167] is a prospective, randomized, open-label phase IIb study. Patients are included at sunitinib initiation while receiving standard schedule 4/2 (50 mg daily) according to the marketing authorization indication. When a dose adjustment of sunitinib is required, patients are randomized between standard schedule 4/2 (37.5 mg daily) and experimental schedule 2/1 (50 mg daily). Key eligibility criteria are the following: patients with locally advanced inoperable or MRCC who are starting first-line treatment with sunitinib, with histologically or cytologically confirmed renal cancer clear cell variant or with a clear cell component, and with Karnofsky performance status ≥70%. The primary objective is to assess the median duration of sunitinib treatment (DOT) in each group. The key secondary objectives are progression-free survival, overall survival, time to randomization, objective response rate, safety, sunitinib dose intensity, health-related quality of life, and the description of main drivers triggering randomization. We hypothesized that experimental schedule 2/1 would result in an improvement in median DOT from 6 to 8.5 months. It was estimated that 112 patients would be needed in each arm during 24 months. In order to take into account the possibility of treatment discontinuation before randomization, 248 patients are necessary.

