**Fig. 1 Fig1:**
[figure not shown]
Trial design

The aim of this randomized clinical trial is to establish whether experimental schedule 2/1 is acceptable in terms of efficacy and toxicity. The main hypothesis is that experimental schedule 2/1 may maintain efficacy in terms of duration of treatment, survival rate, and response rate, has less toxicity, and preserves HRQoL.

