## Discussion

At the time this manuscript was written, 80 patients have been included in the SURF trial, which makes it the largest prospective cohort of patients assessing the question of alternative schedule 2/1 of sunitinib. In comparison to the current available data, this trial will be able to provide more robust data about an alternative schedule of sunitinib based on an academic study.

The SURF trial is asking a pragmatic question adapted to the current practice: what is the best way to adapt sunitinib when side effects occur? In the SURF trial, randomization does not occur at the start of sunitinib but when a dose modification is required. The decision to randomize the patient is based on the choice of the physician. The purpose of the SURF trial is to bring robust prospective data of efficacy and side effects that can sustain the use of alternative schedule 2/1 in clinical routine practice. Furthermore, HRQoL data evaluated by the EORTC QLQ-C30 questionnaire will bring patient perspective on the alternative schedule.

One of the limitations of this design is a potential loss of power depending on the number of patients who may leave the study before randomization. We estimated that 10% of the patients could be lost between the initiation of the treatment and a potential randomization.

Recently, the FDA [17] approved sunitinib in an adjuvant setting for high-risk patients following the results of the S-TRAC trial, showing that sunitinib improved PFS in high-risk patients [18]. In this trial, patients started sunitinib at 50 mg with schedule 4/2. When toxicity occurred, dose interruptions or dose reductions to 37.5 mg per day were allowed, depending on the type and severity of the toxicity. An alternative schedule was not allowed. In the sunitinib arm, 48.8% of patients had grade III adverse events and 12.1% grade IV adverse events. Furthermore concerning HRQoL, on most QLQ-C30 subscales, patients in the sunitinib group had lower scores than those in the placebo group. Dose reductions and interruptions because of adverse events occurred in 34.3% and 46.4%, respectively, of the patients in the sunitinib group, and treatment discontinuations owing to adverse events occurred in 86 patients (28.1%) in the sunitinib group. In this setting, improving the management of side effects and maintaining HRQoL will be a high-priority topic.

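### The hypothesis is comparative, but the only formal test sets a median against a fixed 6 months, and the planned between-arm hazard ratio has no role in the conclusion.

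*Protocol article*

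**What the plan says.** **The claim.** The Abstract (Methods/design) says: "We hypothesized that experimental schedule 2/1 would result in an improvement in median DOT from 6 to 8.5 months". The Discussion puts the trial's question as "what is the best way to adapt sunitinib when side effects occur". Study design, in the text after Fig. 1, words it differently again: "The main hypothesis is that experimental schedule 2/1 may maintain efficacy in terms of duration of treatment".

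**The test.** Under Sample size the objective is per arm: "The main objective of this randomized phase II trial is to evaluate the median DOT in each arm". The hypotheses are "H0 (null hypothesis of inefficiency): median DOT of 6 months [15, 16] and H1 (alternative efficiency hypothesis): median DOT of 8.5 months", and "A Brookmeyer-Crowley type of test will be used to estimate the median". The settings are one-sided 5%, 80% power, 112 patients per arm, 24 months of accrual, at least 12 months of follow-up, and rejection above about 7.66 months.

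**The comparison.** Analyses of time-to-event data excludes P values and states that "the effect size of treatment will be assessed using the HR with its confidence interval". No between-arm hypothesis, threshold or decision rule appears.

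**Related definitions.** Primary endpoint counts DOT from sunitinib initiation. Patients are randomised later, when an adjustment is needed, and one minimisation factor is whether that happens before 6 months or at 6 months or later. Time from randomisation to discontinuation is already a secondary endpoint. Study duration sets the final analysis at 112 events, without saying whether per arm or in total.

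**The concern.** A one-sample test against 6 months shows whether an arm's median exceeds 6 months. It cannot show that 2/1 improves on 4/2. If patients in this trial stay on treatment longer than the historical 6 months for any reason, both arms can pass, and the 2/1 result could then be read as the improvement that the Abstract predicts.

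The benchmark is also exposed to selection. Only patients still on sunitinib when they need an adjustment are randomised, and the time before randomisation counts towards DOT. Everyone randomised at 6 months or later has a DOT of at least 6 months whatever the schedule. A concurrent comparison is protected from this because both arms share the selection. A fixed benchmark is not.

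**Working it through.** **1. Is 112 per arm a one-sample figure?** Inputs from Sample size: medians 6 and 8.5 months, one-sided 5% (z = 1.645), power 80% (z = 0.842). Assume exponential DOT; nobody is censored before 12 months.

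- Proportion still on treatment at 6 months: 0.50 under H0; 2^(-6/8.5) = 0.613 under H1.
- n = (1.645 + 0.842)² × 0.613 × 0.387 / (0.613 - 0.50)² = 115 with unrounded inputs. Other standard variants give 107 to 119.
- Critical value, linear scale with equal variances: 6 + 2.5 × 1.645/(1.645 + 0.842) = 7.65 months, against the stated 7.66.

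So 112 is the size for one arm against a fixed value.

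**2. How often would 2/1 be called effective when the arms do not differ?** On the log-median scale, SE = 1/(ln 2 × √112) = 0.1363. The chance of passing cut-off c at a common true median m is 1 - Φ(ln(c/m)/0.1363). Take c as the stated 7.66, or 7.51, which gives exactly 5% on this scale (6 × exp(1.645 × 0.1363)). The values of m are assumptions.

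| Common true median | c = 7.66 | c = 7.51 |
|---|---|---|
| 6 months | 3.7% | 5.0% |
| 7 months | 25% | 30% |
| 8 months | 62% | 68% |

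**3. How far could the later-randomised stratum move this?** Let a fraction f be randomised at 6 months or later, and let the rest have a median of exactly 6. Both are assumptions; the document does not give the stratum's size. Then the proportion on treatment at 6 months is S = 0.5 + 0.5f in either arm. H0 is rejected when the estimate exceeds 0.5 + 1.645 × 0.5/√112 = 0.578, with probability Φ((S - 0.578)/√(S(1 - S)/112)).

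| f | S | Chance of passing |
|---|---|---|
| 5% | 0.525 | 13% |
| 10% | 0.550 | 28% |
| 15% | 0.575 | 48% |
| 20% | 0.600 | 68% |

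**4. What would the same patients give in a direct comparison?** HR = 6/8.5 = 0.706, |ln HR| = 0.348. With uniform accrual over 24 months and 12 months more, the event probability is 1 - (e^(-12λ) - e^(-36λ))/(24λ), where λ = ln 2/median. This gives 0.915 at a median of 6 and 0.835 at 8.5. Events: 112 × (0.915 + 0.835) = 196.

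- Events for 80% power, one-sided 5%: 4 × (1.645 + 0.842)²/0.348² = 204.
- Power = Φ(√events/2 × 0.348 - z):

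| Total events | One-sided 5% | Two-sided 5% |
|---|---|---|
| 112 | 58% | 45% |
| 196 | 78.6% | 68% |

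Log-rank simulation (8,000 runs) gave 78.7% one-sided with a mean of 196 events.

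**5. How far does 79% depend on its assumptions?** The 6 and 8.5 months run from initiation, so using their ratio after randomisation is an assumption. With an illustrative fixed 2-month shared lead-in, the medians after randomisation are 4 and 6.5 (HR 0.615), and simulated power is about 97%. In the other direction, Sample size enrols 248 before randomisation. If only half were randomised (124), events would be 62 × (0.915 + 0.835) = about 109 and power about 57%.

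**The case against.** The strongest reply is that this is a coherent non-comparative randomised phase II design. The objective, the per-arm sample size, the one-sample test and the absence of P values fit together, and the aim in Study design is only to establish whether 2/1 is acceptable. The question about the best way is posed in the Discussion, not among the objectives. Such designs are legitimate, so having no between-arm test is not an error in itself. What does not survive is the Abstract's hypothesis, which is specific to 2/1 and worded as an improvement. The planned test cannot address it, and nothing limits the conclusion accordingly.

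A reader might infer that the control arm is ignored altogether. The document does not support that: an HR with a confidence interval and medians for both arms will be reported, so a 2/1 arm doing worse would be visible. What is missing is a role for that comparison in the conclusion.

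A reader might also take the 25-68% as inflated type I error. It is not. If the true median is 7 or 8 months, rejecting 6 is correct. The error arises only when the result is read as 2/1 beating 4/2.

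Finally, changing the primary analysis is more than a change of wording. The event trigger has to move too, and 80 patients were already included when the article was written.

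**Conclusion.** The concern holds in this form: the stated hypothesis is comparative, the only formal test is not, and the planned HR carries no weight in the conclusion. With no difference between arms, 2/1 could be called effective with probability of about 25-30% at a common median of 7 months and 62-68% at 8. This rests on 112 per arm, exponential times and assumed true medians. The selection effect is certain in kind for patients randomised at 6 months or later, but its size is unknown, and the stratum figures above are illustrations.

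It would be tempting to say that the existing sample gives 79% power for a direct comparison without further conditions. The documents do not support that. The figure needs one-sided 5%, 224 patients actually randomised, about 196 events, exponential times, and the 6:8.5 ratio holding after randomisation. It falls to 68% at two-sided 5%, and to 58% if the 112 events under Study duration are a total.

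**What to change.** Base the efficacy conclusion on the randomised comparison:

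- **Primary analysis:** time from randomisation to discontinuation, by log-rank and Cox, stratified by the minimisation factors other than centre (time to randomisation and Heng group), at one-sided 5%, with the HR and its 90% confidence interval. An upper limit below 1 corresponds to the one-sided 5% test, so the conclusion can be read from the interval without reporting a P value.
- **Per-arm medians:** keep them, with confidence intervals, as descriptive.
- **Hypothesis:** state one, improvement, in the same terms in the Abstract, Study design and Sample size.
- **Trigger:** replace the unspecified 112 events under Study duration with about 196-204 total events.
- **Power:** state it as conditional: about 79% at one-sided 5% (68% two-sided) with 224 randomised, about 196 events and HR 0.706 after randomisation; about 58% at 112 total events.

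The cost is an amendment to the primary analysis and event trigger, and a stated power slightly below 80%. No new data item is needed, since the endpoint is already secondary and the HR is already planned.

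If the non-comparative design is kept instead, the Abstract and Discussion must drop the comparative claim.
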